**6. N Collection of data from voice, video, digital, or image recordings made for research purposes.**

**7. Y Research on individual or group characteristics or behavior(including, but not limited to, research on perception, cognition, motivation, identity, language, communication, cultural beliefs or practices, and social behavior) or research employing survey, interview, oral history, focus group, program evaluation, human factors evaluation, or quality assurance methodologies. (NOTE: Some research in this category may be exempt from the HHS regulations for the protection of human subjects. 45 CFR 46.101(b)(2) and (b)(3). This listing refers only to research that is not exempt.)**

## 1. Purpose

**a) In layperson's language state the purpose of the study in 3-5 sentences.**

Over 30 million surgeries are performed annually in the US. Up to 30% of surgical patients experience delayed surgical recovery, marked by prolonged post-surgical pain, opioid consumption, and functional

**Title :** Immune system modulation by enhanced vs standard prehabilitation program in patients undergoing elective major surgery - a prospective monocentric randomized single-blinded control . . .

**Approval Period:** 10/23/2023 - 12/31/2999

impairment, which contributes \$8 billion annually to US health care costs. Novel interventions that improve the resolution of pain, minimize opioid exposure, and accelerate functional recovery after surgery are urgently needed.

Multi-modal pre-operative optimization programs (or "prehab") integrating exercise, nutrition, and stress reduction have been shown to safely and effectively improve outcomes after surgery. However, we lack objective biological markers to assess prehab effectiveness and to tailor prehab programs to individual patients. Surgery is a profound immunological perturbation, during which a complex network of innate and adaptive immune cells is mobilized to organize the recovery process of wound healing, tissue repair, and pain resolution. As such, the in-depth assessment of a patient's immune system before surgery is a highly promising approach to identify biological markers for accurate risk prediction.

**b) State what the Investigator(s) hope to learn from the study. Include an assessment of the importance of this new knowledge.**

The investigators hope to determine whether a personalized health optimization program combining one-on-one coaching, tailored to each patient ("surge") is able to enhance patient's immune state in comparison to unpersonalized prehabilitation ("standard rehabilitation") before surgery

The importance of this new knowledge is better understanding of ways that we can improve outcomes, engagement, experience and overall long-term health of patients undergoing major abdominal operations. This would translate to increased healthcare value and better long-term outcomes.

**c) Explain why human subjects must be used for this project. (i.e. purpose of study is to test efficacy of investigational device in individuals with specific condition; purpose of study is to examine specific behavioral traits in humans in classroom or other environment)**

The purpose of the study is to determine the effect on immune cells of a personalized prehabilitation intervention in adults undergoing elective major abdominal surgery.

## 2. Study Procedures

**a) Please SUMMARIZE the research procedures, screening through closeout, which the research participant will undergo. Sections in the protocol attached in section 16 can be referenced, BUT do not copy the clinical protocol. Be clear on what is to be done for research and what is part of standard of care. For research involving collaborators, please specify the respective roles of Stanford and each collaborator on the protocol.**

Standard prehabilitation:

Patients will be provided with standard instructions in a hard-copy form specific to prehabilitation before surgery associating physical, nutritional, stress-reduction and cognitive recommendations without any personalized coaching for at least 3 weeks prior to surgery (see attached ControlGroup\_ProgramBook document).

Research Activities:

---

**Title :** Immune system modulation by enhanced vs standard prehabilitation program in patients undergoing elective major surgery - a prospective monocentric randomized single-blinded control . . .

**Approval Period:** 10/23/2023 - 12/31/2999

---

1. Screening: The research team will identify eligible patients by screening the clinic schedules of general surgeons.

2. Study Enrollment: Either in person during their surgical clinic visit, or by phone at least 28 days before surgery. If patients accept to be included, they will be randomized.

3. Baseline assessment (Day 0): Nutritional (using the Mediterranean Diet Scale), physical (by measuring 6 min walk test, Timed up and go, Five Times Sit to Stand Test and Wall Squat Tests), cognitive (using the qMCI test), anxiety (using the APAIS scale and the Pain Catastrophizing Scale) and quality of life status (using the SF36-scale) at baseline (prior to prehabilitation) will be recorded on RedCap by a personnel previously trained to the achievement of tests of the study.

4. Prehabilitation: SURGE or standard program will be proposed to the patients for 3-6 weeks.

SURGE consists in a 6-session (over 3-6 weeks) personalized prehabilitation program. This program will be delivered remotely with 2 in person (with a trained member of the research team) sessions every week. Self-exercises will be promoted every day.

>> Exercise Component: participants will have the opportunity to make a personalized plan with a member of the research team (SURGE) for physical exercise. First, an evaluation of patient's aerobic capacity, functional mobility, functional strength, ambulation, fall risk, and overall mobility using validated outcome measures and movement analysis will be done by a trained member of the research team. Based on their functional level and preexisting conditions, therapeutic exercises will be recommended to optimize their strength, endurance, flexibility, and functional mobility in preparation for surgery. Therapeutic exercises may include gait training, strengthening exercises, flexibility exercises/stretching, movement pattern training, relaxation techniques, neuromuscular re-education, breathing strategies, movement strategies, and transfer training (i.e. bed mobility). Decisions about the interventions are based on the assessment, individual patient characteristics, environmental factors (i.e. space limitations), surgical type, and monitoring of the client's response and progress. Weekly sessions are 30-45 minutes long to monitor the client's response and progress their program. Based on their response to exercise (evaluated also by one app: Timed Walk App), re-evaluation via the assessments described above, change their plan of care (alter frequency, resistance, exercises) or discontinuation of treatment could be decided.

>> Nutrition Component: participants will have the opportunity to make a personalized plan for improving their diet with a member of the research team (SURGE). It will involve transitioning the patient to the Mediterranean diet with targets regarding hydration and the proportion of fruits, vegetables, whole grains, and healthy fats the patient will consume in a given day. This nutritional program is flexible, and it allows for specific physician and nutritionist-recommended dietary needs to be incorporated. The patient is also given tools to encourage success in healthier eating, including recipes, sample menus, healthy restaurant options, meal kit options, and local CSA box options.

**Title :** Immune system modulation by enhanced vs standard prehabilitation program in patients undergoing elective major surgery - a prospective monocentric randomized single-blinded control . . .

**Approval Period:** 10/23/2023 - 12/31/2999

>> Cognition component: participants will have the opportunity to make a personalized plan for improving their cognition with a member of the research team (SURGE). It will consist on the daily use of Lumosity training program (<https://www.lumosity.com/>), an already existing free of charge app built to increase memory skills and used in the perioperative context. The program proposed by Lumosity is tailored to each patient. The use of Lumosity will be monitored at each in person session. Patients will be expected to complete at least three 5 minute sessions of Lumosity training per day. No information will be collected by the company.

>> Stress-reduction component: participants will have the opportunity to learn techniques for mindfulness that have been established to reduce stress and assist with pain management with a member of the research team (SURGE). Patients will be offered to listen to audio recording of relaxation sessions. Each session contains a relaxation technique that the patient practices while listening to the recording. Then the technique is used the next as a baseline to introduce a new technique more advanced. For some patients who struggle with the techniques the program will be adapted. Patients will choose with 2 or 3 techniques and work on them.

5. Every 7 days, whatever the arm, a compliance questionnaire will be filled by phone, by trained members of the research team blinded to the treatment arm of the study and collected in RedCap

6. End of prehabilitation program: Nutritional (using the Mediterranean Diet Scale), physical (by measuring 6 min walk test, Timed up and go, Five Times Sit to Stand Test and Wall Squat Test), cognitive (using the qMCI test), anxiety (using the APAIS scale and the Pain Catastrophizing Scale) and quality of life status (using the SF36-scale) at the end of the prehabilitation program will be recorded on RedCap by a personnel previously trained to the achievement of tests of the study.

7. Surgery

8. Post-operative period:

>> From surgery end to discharge from the hospital, length of stay, pain and adverse clinical events will be measured and recorded on RedCap.

>> Cognitive function (using qMCI), neuropathic pain (using the DN-4 scale) and quality of life (using SF-36 scale) will be assessed 30 days after surgery and recorded on RedCap.

**b) Explain how the above research procedures are the least risky that can be performed consistent with sound research design.**

These research procedures pose minimal risk to the patient, as the exercises are tailored for patients' baseline level of fitness, nutritional, cognitive and anxiety status to reduce the risk of injury. Moreover prehabilitation has been demonstrated to be safe and beneficial to surgical outcomes.

**c) State if deception will be used. If so, provide the rationale and describe debriefing procedures. Since you will not be fully informing the participant in your consent process and form, complete an alteration of consent (in section 13). Submit a debriefing script (in section 16).**

**Title :** Immune system modulation by enhanced vs standard prehabilitation program in patients undergoing elective major surgery - a prospective monocentric randomized single-blinded control . . .

**Approval Period:** 10/23/2023 - 12/31/2999

Deception will not be used.

- d) State if photo, audio or video recording will occur. Describe what will become of the photos or recording after use, e.g., shown at scientific meetings, erased. Describe the final disposition of the recordings.**

Audio/video recording will not occur.

- e) Describe alternative procedures or courses of treatment, if any, that might be advantageous to the participant. Describe potential risks and benefits associated with these. Any standard treatment that is being withheld must be disclosed in the consent process and form. (i.e. standard-of-care drug, different interventional procedure, no procedure or treatment, palliative care, other research studies).**

There are no proven alternative procedures for Prehab. Standard treatment is not being withheld.

- f) Will it be possible to continue the more (most) appropriate therapy for the participant(s) after the conclusion of the study?**

Patients may choose to continue any/all of the prehab program components as long as they wish.

- g) Study Endpoint. What are the guidelines or end points by which you can evaluate the different treatments (i.e. study drug, device, procedure) during the study? If one proves to be clearly more effective than another (or others) during the course of a study, will the study be terminated before the projected total participant population has been enrolled? When will the study end if no important differences are detected?**

The endpoints we will use to evaluate the adherence to prehab programs (compared to one arm to the other) will compare before and after prehab program time and are:

- > Adherence to prehab programs using a modified "Rehabilitation Adherence Measure for Athletic Training" scale
- > Physical status assessment including 6 Minute Walk Test (6MWT), Timed Up and Go (TUG), Five Times Sit to Stand Test & Wall Squat Test and Body Mass Index (BMI)
- > Prevalence and global severity of anxiety using questionnaires such as the APAIS (Amsterdam Preoperative Anxiety and Information Scale) and the Pain catastrophization scale.
- > Cognitive status evaluated by the qMCI

We will also evaluate the effect of prehab programs on post-operative outcomes by collecting:

- > Hospital length of stay
- > Readmission within 30 days after surgery
- > Postoperative complications scored by the Comprehensive Complication Index (CCI) within 90 days after surgery
- > Inpatient opioid use and pain levels during hospitalization
- > Neuropathic pain, quality of life and cognitive function assessed 30 days after surgery (in comparison to before surgery)

If the intervention is found to be clearly harmful then the study will be terminated before the total projected participant population has been enrolled. This will be determined by assessing for increase in complication rates after surgery beyond our baseline rates of complications (as determined by NSQIP data). These rates will be

**Title :** Immune system modulation by enhanced vs standard prehabilitation program in patients undergoing elective major surgery - a prospective monocentric randomized single-blinded control . . .

**Approval Period:** 10/23/2023 - 12/31/2999

calculated on a quarterly basis.

The study will end after complete enrollment (120 patients) or after 16 months of enrollment into the prehab intervention if no important differences are detected.

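### Patients are randomised before the Day 0 baseline tests, and nothing states that the allocation is withheld until those tests are recorded

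*Protocol*

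**What the plan says.** Section 2(a) of the protocol numbers the procedures.

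- **Step 2, enrolment.** It takes place "Either in person during their surgical clinic visit, or by phone at least 28 days before surgery", and then: "If patients accept to be included, they will be randomized".
- **Step 3, Day 0.** The tests come next: "Baseline assessment (Day 0): Nutritional (using the Mediterranean Diet Scale), physical (by measuring 6 min walk test, Timed up and go", followed by sit-to-stand, wall squat, qMCI, APAIS, the Pain Catastrophizing Scale and SF-36. Timing is given relative to the programme, not to randomisation: "quality of life status (using the SF36-scale) at baseline (prior to prehabilitation) will be recorded on RedCap by a personnel previously trained".
- **Step 4.** The SURGE or standard programme starts.
- **Step 5.** The weekly compliance questionnaire is taken "by trained members of the research team blinded to the treatment arm of the study".
- **Step 6.** The Day 0 tests are repeated at the end of the programme.

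Staff at steps 3 and 6 are described by their training only: "will be recorded on RedCap by a personnel previously trained to the achievement of tests of the study". The title calls the trial "prospective monocentric randomized single-blinded control" but does not name the blinded party.

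Section 2(g) says that the programme endpoints "will compare before and after prehab program time", between arms. It lists adherence, the physical tests with BMI, anxiety and catastrophizing, and qMCI. It also compares neuropathic pain, quality of life and cognition at 30 days with the state before surgery.

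**The concern.** A baseline protects a before/after comparison only if it cannot depend on the arm. Here it is measured after the arm has been drawn. The measures are effort-dependent (walk, sit-to-stand, wall squat), self-reported (APAIS, catastrophizing, SF-36) or administered by an assessor (qMCI). The arms differ visibly: one gets one-to-one coaching, the other a booklet. A patient told of the booklet may report more anxiety on Day 0. An assessor who knows the arm may accept a weaker first effort. The Resources section (Qualified staff) lists data collection and coaching as tasks of the same group of people, so the protocol does not separate the two roles.

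The second risk is loss. A patient who leaves before randomisation cannot unbalance the arms. A patient who leaves between randomisation and Day 0 can, and has no baseline.

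**Working it through.** **Order and blinding.** Steps 2 and 3 put randomisation before baseline, and no other section reverses this. The only staff called blinded to arm are the weekly callers in step 5. No text says when patient or assessor learns the allocation, and no interval between steps 2 and 3 is given. The physical tests can hardly be done in a phone call, so some interval is likely for patients enrolled that way.

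**Which endpoints use Day 0.**

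- They do: the physical, anxiety and cognitive endpoints.
- They may: quality of life and cognition at 30 days. SF-36 and qMCI are taken both at Day 0 and at the end of the programme, and section 2(g) does not say which is the reference.
- They do not: adherence, length of stay, readmission, complications, and inpatient opioid use and pain.

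**Illustration of size.** The protocol gives no significance level, SD, effect size, allocation ratio or dropout rate, so there is no figure of its own to reproduce. From the protocol: 120 patients. Assumed: 1:1 allocation, so n = 60 per arm; two-sided 5% test; no true effect; before/after correlation ρ of 0.5 or 0.7; a shift δ of 0.1 to 0.3 SD in one arm's baseline only, gone by the end-of-programme test.

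- Change score: bias δ in size, SE = √(2(1−ρ)) × √(2/n).
- Baseline-adjusted (ANCOVA): bias ρδ in size, SE = √(1−ρ²) × √(2/n).
- False-positive rate = 1 − Φ(1.96 − bias/SE) + Φ(−1.96 − bias/SE).

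Example with ρ = 0.5 and δ = 0.2, change score: SE = 1 × √(2/60) = 0.183; bias/SE = 0.2/0.183 = 1.095; rate = 1 − Φ(0.865) + Φ(−3.055) = 0.195.

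| ρ | δ (SD) | Change score | Baseline-adjusted |
|---|---|---|---|
| 0.5 | 0.1 | 8.5% | 6.2% |
| 0.5 | 0.2 | 19.5% | 9.7% |
| 0.5 | 0.3 | 37.6% | 15.8% |
| 0.7 | 0.1 | 10.9% | 8.4% |
| 0.7 | 0.2 | 29.3% | 18.9% |
| 0.7 | 0.3 | 56.4% | 36.4% |

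Adjustment reduces the effect but does not remove it.

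**If the shift persists.** With the same δ at both times, the change-score bias is δ − δ = 0 and the rate returns to 5%. A baseline-adjusted analysis then has bias (1−ρ)δ. That bias comes from the shifted end-of-programme score, which the order of steps 2 and 3 does not control.

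**Loss before Day 0.** Assumed losses of 5% and 15% would leave 60 × 0.95 = 57 and 60 × 0.85 = 51 patients with a baseline. The protocol gives no rate from which to estimate the real loss.

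**Room in the calendar.** 28 days minimum lead time − 21 days minimum programme = 7 days.

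**The case against.** The strongest reply is that contamination is inferred. The protocol says when patients are randomised, not when anyone is told. Day 0 could fall on the day of a clinic enrolment, the trial is labelled single-blinded, and the section is a summary field on an ethics form. This stands as a limit: a reader might infer that patients and assessors know the arm at Day 0, and the document does not say so. It does not dispose of the point, because the document does not say the opposite either, and the label names nobody.

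Second, the table depends on a shift that is present at Day 0 and gone by the end. Patients in both arms know what they received by then, so the shift might persist and cancel in a change score. The 0.1 to 0.3 SD range has no source in the protocol. The plausible mechanisms also pull in opposite directions: extra Day 0 anxiety in the booklet arm flatters the booklet, whereas under-scoring the start of coached patients flatters SURGE. All of this stands. The percentages are not an estimate of this trial's error rate.

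Third, the stated purpose is the effect on immune cells, and most postoperative outcomes need no Day 0 score. This also stands and narrows the scope.

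Fourth, reordering does not cure dropout. A patient who leaves after learning the arm still has no end-of-programme value, and the treatment of missing values may be set out in an analysis plan that is not shown. This is correct. The order of the steps, however, is trial conduct: an analysis plan cannot restore a clean baseline or supply one never taken.

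**Conclusion.** The point holds within these limits. The order (randomise, then measure baseline) is explicit, and no safeguard is stated. The measures exposed are the before/after physical, anxiety and cognitive endpoints, and the 30-day quality-of-life and cognition comparisons where Day 0 is their reference. Patients lost before Day 0 have no baseline.

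The documents do not support saying that the baseline is biased, that the bias favours a particular arm, that all endpoints are compromised, or that the trial's false-positive rate is 9% to 56%. That range is what a transient, baseline-only shift of 0.1 to 0.3 SD would produce in a change score under the assumptions listed. With a shift that persists equally the rate is near 5%. The case for changing the order is that the risk can be avoided at almost no cost, not that its size is known.

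**What to change.** Rewrite steps 2 and 3 of section 2(a) in this order: consent, Day 0 assessments, randomisation, programme. Define baseline as the last value before randomisation. If the order must stay, state at minimum that the allocation is concealed from patient and assessor until Day 0 is recorded, and say whom the single-blinded label covers.

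Reordering gives every randomised patient a baseline that the arm cannot have influenced. Concealment alone protects the values, but patients lost before Day 0 would still have none. Neither change deals with dropout after allocation, so randomised patients with missing end-of-programme values still need a stated analysis.

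The cost is protocol wording and a short wait. No visit or test is added, since Day 0 already precedes the programme. The allocation has to wait for Day 0, including for patients enrolled by phone. For those enrolled at the 28-day minimum this must fit in the roughly 7 days beyond the 3-week minimum programme, which also have to hold the end-of-programme assessment. A programme longer than 3 weeks leaves less room.

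### Day-30 neuropathic pain is to be compared with before surgery, but no DN-4 is scheduled before surgery; the reference for SF-36 and qMCI and the contrast for adherence also need stating

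*Protocol*

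**What the plan says.** Protocol, section 2, part g (Study Endpoint) gives two lists of endpoints.

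- The first list is introduced by saying that the endpoints "will compare before and after prehab program time and are" the items that follow. Adherence is the first item. The same sentence also says that one arm is compared with the other.
- The second list covers post-operative outcomes and includes "Neuropathic pain, quality of life and cognitive function assessed 30 days after surgery (in comparison to before surgery". It does not say which pre-operative visit is meant.

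Section 2, part a gives the assessments:

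- Step 3 (Day 0) includes "cognitive (using the qMCI test), anxiety (using the APAIS scale and the Pain Catastrophizing Scale) and quality of life status (using the SF36-scale) at baseline", alongside the diet scale and physical tests. This visit is labelled as preceding prehabilitation.
- Step 5 collects compliance by phone every 7 days in both arms.
- Step 6 repeats the Day 0 instruments, including "anxiety (using the APAIS scale and the Pain Catastrophizing Scale) and quality of life status (using the SF36-scale) at the end of the prehabilitation program".
- Step 8 states "Cognitive function (using qMCI), neuropathic pain (using the DN-4 scale) and quality of life (using SF-36 scale) will be assessed 30 days after surgery".

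**The concern.** An endpoint defined against an earlier value needs that earlier value to be collected. DN-4 appears in the schedule only after surgery, so the comparison has no first term. Unlike most questions of analysis, this one cannot be repaired once patients have passed the visit.

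The eligible operations in section 8, part h are broad and include thoracic, gynecologic, plastic and neurosurgical procedures. Some patients may well have neuropathic pain beforehand; the protocol gives no figure for how many. A day-30 score alone mixes that pain with pain that began after the operation, and the comparison with before surgery is what would have separated them.

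Two neighbouring statements have a related but milder weakness. SF-36 and qMCI are measured twice before surgery, once before and once after the programme, and the endpoint wording fits either. Adherence has no value before the programme starts, yet it heads a list of before/after contrasts.

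**Working it through.** The protocol gives no figure for these contrasts, so there is none to reproduce. The check sets the endpoint wording against the assessment schedule.

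**Step 1. Which values exist (section 2, part a)**

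| Measure | Day 0 (step 3) | End of prehabilitation (step 6) | Day 30 (step 8) |
|---|---|---|---|
| DN-4 | not listed | not listed | listed |
| SF-36 | listed | listed | listed |
| qMCI | listed | listed | listed |

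Adherence is collected every 7 days during the programme (step 5).

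**Step 2. DN-4.** There are 0 assessments before surgery and 1 after. A comparison of day 30 with before surgery needs at least one of each, so it is not computable from the schedule as listed. The Pain Catastrophizing Scale is in both pre-operative batteries, but it is listed there under anxiety and is not a neuropathic pain measure.

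**Step 3. SF-36 and qMCI.** Let *a* be the between-arm difference (SURGE minus standard, higher is better) at the end of prehabilitation and *b* the difference at day 30. Randomisation makes the expected difference at Day 0 zero. Then:

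- change from Day 0 has expected contrast *b* − 0 = *b*;
- change from the end of prehabilitation has expected contrast *b* − *a*.

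The protocol gives no effect sizes. The values below are assumptions in SD units, chosen to show the range:

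| *a* | *b* | From Day 0 | From end of prehabilitation |
|---|---|---|---|
| 0.3 | 0.5 | 0.50 | 0.5 − 0.3 = 0.20 |
| 0.5 | 0.5 | 0.50 | 0.5 − 0.5 = 0.00 |
| 0.5 | 0.3 | 0.30 | 0.3 − 0.5 = −0.20 |

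In each row the later reference removes exactly the gain made before surgery. A gain in qMCI before surgery is plausible because the SURGE programme includes daily cognitive training between the two pre-operative visits (section 2, part a, step 4).

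**Step 4. Adherence.** There are 0 values before the programme and weekly values during it. A before/after contrast has no first term. A between-arm contrast of the weekly scores is computable.

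**The case against.** **The form is a summary.** Section 2, part a asks applicants to summarise procedures and not to copy the clinical protocol, so the batteries may not be exhaustive. BMI supports this: it is in the before/after list in part g and is missing from both pre-operative batteries too. The DN-4 form is an attachment (section 16), and its full schedule is not visible. This stands in part. A reader might infer that none of the 120 patients will ever have a pre-surgical DN-4, which is firmer than a summary form supports. What the document does show is an endpoint that its own schedule, as listed, cannot supply.

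**The consequence is limited.** This is one item among several post-operative outcomes, and the randomised comparison of day-30 DN-4 needs no baseline to be valid. This stands, and it is why the second option in the fix is acceptable.

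**The SF-36 and qMCI point is an ambiguity.** The protocol never selects the end-of-prehabilitation value. It collects a Day 0 value and calls it baseline, and an analysis plan could name it as the reference. Change from the end of prehabilitation also answers a legitimate, different question about perioperative decline. All of this stands. A reader might go further and infer that SURGE will look worse after surgery the better it worked. That does not follow: the contrast *b* − *a* is negative only if the gain fades by day 30, zero if it persists and positive if it grows.

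**No estimator is fixed.** A reader might infer that the plan commits to change scores and so loses precision against ANCOVA. The wording is compatible with baseline adjustment, and any figure for the loss would rest on a correlation the document does not give. This is not part of the defect.

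**Adherence is loose drafting.** Part g mentions comparison between arms, and section 3, part a gives comparing compliance of the two programmes as an aim. The intended analysis is evident, so only the wording is at fault.

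**Conclusion.** The DN-4 mismatch holds. The endpoint and the listed schedule contradict each other, and the stated contrast cannot be computed from the data as scheduled. The conclusion assumes that the listed batteries are complete for DN-4. If a fuller schedule already includes it, the remedy is only to say so here.

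The effect on the trial is moderate: one secondary contrast is lost, along with the ability to distinguish new from pre-existing neuropathic pain, while the between-arm comparison at day 30 survives. What raises it above a wording matter is that a value not collected cannot be recovered at analysis.

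The other two parts are clarifications. For SF-36 and qMCI, taking the end of prehabilitation as reference would understate the day-30 effect by whatever benefit was already present before surgery; the protocol permits that reading but does not adopt it. For adherence, the comparison the investigators want is available and only needs to be stated correctly.

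**What to change.** 1. **DN-4.** Add it to the Day 0 battery in section 2, part a, step 3, and adjust the day-30 between-arm comparison for it. Failing that, remove the before-surgery comparison for neuropathic pain in part g and compare day-30 DN-4 between arms only. Patients already past Day 0 when the change is made would have no baseline, so if enrolment is well advanced the second option is the workable one.
2. **SF-36 and qMCI.** State in part g that the Day 0 value, taken before prehabilitation, is the reference for the day-30 comparisons.
3. **Adherence.** Take it out of the before/after list and state it as a between-arm comparison of the weekly scores.

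The cost is one short questionnaire at a visit that already takes place, plus wording. Under the second option for DN-4 the cost is wording alone.
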